### Ethics

The Danish Data Protection Agency approved of the study (journal number: 2007-41-0530). The Scientific Ethical Committee of the Capital Region in Denmark decided that according to Danish law, the project should not be submitted to the committee (journal number H-A-2007-0019). Informed consent to use the collected data for research purpose was obtained from all participant’s parents.

### Future follow-up

Future weight development will be followed for participating children in the intervention and both control groups by first linking the CPR-numbers to the school-health records (heights and weightsare measured at enrolment (age 6–8 years), midway (age 10–12 years), and at termination (age 14–16 years)), then to draft board records for the males (draft board examinations are mandatory in Denmark, and includes, among others measurement of heightsand weights) and to the Danish National Birth Registrywhere information on weights and heights can be obtained, because pre-pregnancy weights and heights is recorded during the first 6–10 weeks of all pregnancies. Thus, the project has important potential for evaluating the long-term effects of the intervention.

## Discussion

This primary intervention study described in this paper aims to prevent development of overweight among those children aged 2–6 years, who are still normal weight but also are at high risk of future overweight, because of either a high birth weight, having a mother who was overweight prior to pregnancy, or having a mother with low educational level. The study is considered to be the first to perform an intervention focusing on young high-risk children. Additionally, it is also among the first studies to intervene not only by improving diet and physical activity habits, but also by optimizing sleep quality and quantity, and reducing stress levels. Finally, few prior studies considered normal weight children only, but included both normal and overweight children in their interventions.

Our study will be able to assess not only the short-, but also the long-term effects of an early intervention, due to the possibility to link the participants’ CPR-numbers to relevant Danish registers, with information on weight development during school years and way into adolescence and adulthood.

The limitations of the study include attrition bias, since it is likely that the most resourceful families will remain in study. This will be explored by describing attrition according to maternal BMI and SES, and the child’s birth weight which are known for both participants and non-participants. Randomization should eliminate the problem with a lower than expected participation rate. However, it may inflate observed differences between intervention and control group since the participating families may be those who already focus on healthy lifestyles, and who are the most resourceful.

The present study focused on the overweight mothers, and did not consider overweight among fathers. Generally, predisposition to obesity in a child is dependent of whether the mother or the father is overweight or obese, but unfortunately no Danish registers contain information on paternal heights and weights around the time the child was conceived or born, which could have been used for selection of the children predisposed to future overweight in the present study. If the result of the intervention is found to be effective in future, information on familial obesity may be obtained from the public health nurses who have contact with almost all families from birth through 1 year of the child, or through GP’s who generally have contact to families on a regular basis including during the child’s first years of life. Also, the mandatory draft board examinations may be used to identify those fathers who were overweight already at age 19 on average. Finally, school health registries can be used to identify children with overweight siblings.

An important strength of the study is the randomized design and the use of two control groups, which increases the possibility to estimate a true effect of the intervention. This design also makes it possible to evaluate if the simple information to parents that their child is at a high risk of future overweight, is an easy and inexpensive way of preventing some later overweight in the child. Another important strength is the use of hair samples to measure long term stress exposure via cortisol level from around 350 children and 650 parents, which is considered to be one of the largest sample of hair cortisol collected till date.

Indeed, if the intervention proves to be effective, it may easily be integrated into the already established and very efficient Danish visiting nurses system, where families are offered home visits from a nurse and counseling on ex. the child’s well-being, lactation, and development during the child’s first two years of life. It may also be an independent program in municipalities who wish to draw special attention to pre-school children and/or primary prevention of overweight and obesity.

The Danish Board of Technology recently published a report that focused on action on targeted prevention of obesity. It was concluded that “in order to curb the obesity epidemic, effective ….. prevention in yet *normal* weight is needed”. It was summarized that there is a need for improving the effect of obesity prevention in those groups who are at the *highest future risk* of developing overweight and obesity [35], and that future efforts therefore should *target high risk groups* to a higher extent [35]. It is considered that the Healthy Start project is in line with this conclusion, and thus may provide the first important information on the effectiveness of such programs, and if effective, in addition contribute with evidence on how to curb the obesity curve.

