## Methods/design

### Study design

In 2009, data on all births between 01.01.2004 and 31.12.2007 in 11 selected municipalities from the greater Copenhagen area was obtained from the Danish National Birth Registry at the National Board of Health. This register contains information on all births, whether at hospital or home, on factors such as birth weight and length, height and pre-pregnant weight of the mother, parity, and Central Personal Registry number (CPR-number). Data on socioeconomic status (SES) (estimated from maternal educational level) was obtained from the administrative birth forms. This was done manually using the CPR-numbers obtained from the birth register. This showed to require more resources than expected, and it was consequently chosen to select children from low SES families in just one municipality. After selecting the children eligible for participation, the children were allocated to three groups, using computer based randomization stratified on municipality and with simple randomization within strata, and were afterwards identified and invited to participate in the study. All siblings were allocated to the same group.

The three groups were:

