Figure 1 shows the number of participants selected and invited to participate in the Healthy Start project. When planning the project, it was anticipated that about 40% would accept the invitation to participate. However, as shown in Figure 1, the participation rate for the intervention group and the control group was around 21%. The relatively low participation rate may reflect the focus of primary prevention, since it may be difficult to encourage lifestyle changes to parents of a child who is still normal weight, although at increased risk of developing overweight. Furthermore, it was also estimated that a maximum 10% of the participating children would be overweight, but as much as 15% of the children who turned up for the initial examination were already overweight at baseline (Figure 1). Again, this higher proportion may reflect that parents to the overweight children were more willing to show up, because they were aware that their child was at risk. Table 1 shows the baseline distribution of gender, selection on birth weight, selection on maternal pre-pregnancy overweight and selection on low SES.

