#### Stress of the child

To assess behavioral difficulties and stress in the child, the Danish version of the Strengths and Difficulties Questionnaire (SDQ) was included as an integrated part of the parental questionnaire. SDQ is a behavioral screening questionnaire that consists of 25 items on prosocial behavior and emotional and behavior problems. Scores on 5 scales are derived from these 25 items: emotional symptoms (5 items), conduct problems (5 items), hyperactivity/inattention (5 items), peer relationship problems (5 items) and pro-social behavior (5 items) [13]. The SDQ has been translated into the different Nordic languages, and has so far been completed for nearly 100,000 children in the Nordic countries during the past years [14].

Table 2 shows the pre-intervention distribution of age, height, weight, BMI, waist circumference, hip circumference, sum of 4 skinfolds, percentage body fat, energy intake, carbohydrate intake, protein intake, fat intake, sugar intake, sleep latency, SDQ-score, and household income by group. *T*-test analyses showed a statistically significant difference in total SDQ-score between the intervention group and the control group (Table 2). No other significant differences in baseline characteristics between the intervention group and the control group were found (Table 2).

**Table 2 T2:** Pre-intervention distribution of selected covariates by group

	**Intervention group**			**Control group**			**P (**** *t* ****-test)**
	**n**	**Mean**	**SD**	**n**	**Mean**	**SD**	
**Age (years)**	271	4.0	1.1	272	4.0	1.1	1.00
**Height (cm)**	271	104.3	9.2	272	104.5	9.1	0.77
**Weight (kg)**	271	17.4	3.1	272	17.6	3.0	0.45
**BMI (kg/m**^ **2** ^**)**	271	15.9	1.0	272	16.0	1.0	0.12
**Waist circumference (cm)**	253	51.8	3.2	257	52.1	3.0	0.22
**Hip circumference (cm)**	252	55.5	3.6	255	56.0	3.9	0.19
**Sum of 4 skinfolds (mm)**	236	24.6	5.4	242	24.8	5.2	0.67
**Body fat (%)**	199	22.3	10.1	176	21.3	8.9	0.33
**Energy intake (MJ)**	237	4.7	1.0	244	4.8	1.0	0.15
**Carbohydrate intake (gr./day)**	237	158.0	36.0	244	164.1	35.3	0.06
**Protein intake (gr./day)**	237	42.8	11.2	244	44.6	10.3	0.07
**Fat intake (gr./day)**	237	38.1	10.1	244	38.1	11.2	0.96
**Sugar intake (gr./day)**	237	56.2	16.5	244	58.5	16.5	0.12
**Sleep latency (minutes)**	250	18.3	14.5	256	18.6	13.9	0.84
**SDQ-score (points)**	253	7.1	3.9	256	6.4	4.0	0.05*
**Household income (thousands, DKK)**	217	870	622	231	788	306	0.07

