### Power calculation

With a power of 90%, alpha of 0.05 and 275 individuals in each group, it will be possible to detect a difference between the intervention- and control groups of 0.28 SD in BMI. For a 7-year old boy with a height of 1.25 m (equivalent to the mean height for 7-year old children in 1980–1983), a 0.28 SD BMI corresponds to a difference in BMI = 0.45 kg/m^2^, or 0.70 kg body weight between the intervention and control groups. With 80% power and a significance level of 5%, we will be able to demonstrate differences of 0.5 BMI units between the intervention and control group children. We greatly oversampled in relation to the main outcome (BMI) to secure sufficient numbers post-intervention and in relation to more specific outcomes such as body fat and fat free mass.

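### Randomisation cannot remove the low-participation problem, because families chose to take part, and overweight children were screened out, after allocation

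*Protocol article*

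**What the plan says.** The order of events is in the Study design section of the protocol article. Allocation came first: "After selecting the children eligible for participation, the children were allocated to three groups". Contact with families is placed later in the same account, which says that those allocated "and were afterwards identified and invited to participate in the study". Enrolment reports that "the participation rate for the intervention group and the control group was around 21" per cent, whereas at the planning stage "it was anticipated that about 40% would accept the invitation to participate". The descriptions of the intervention and control groups add a second step after allocation: children found overweight at the first visit were excluded. The Abstract counts 92 such children and gives 271 and 272 as the numbers included.

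The Discussion, under limitations, states: "Randomization should eliminate the problem with a lower than expected participation rate". Its next sentence concedes that participation may exaggerate the difference between the arms, because families who take part may already be the more health-minded and better resourced.

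The Power calculation names BMI as the main outcome and says that "it will be possible to detect a difference between the intervention- and control groups of 0.28 SD in BMI". Below its heading on stress of the child, the article compares the arms at baseline by t-test, reports a difference in SDQ score, and adds: "No other significant differences in baseline characteristics between the intervention group and the control group were found". Table 2 there gives baseline BMI as 15.9 (intervention) and 16.0 (control), SD 1.0 in both, P = 0.12.

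**The concern.** Randomisation balances, in expectation, the groups as they were allocated. It does not guarantee balance between subsets formed later by family choice and by a weight screen. The arms led to different commitments: up to 10 consultations plus classes in one, a baseline and a follow-up visit in the other. If families knew this when they accepted, different kinds of family could have come forward in each arm. The sentence in the Discussion therefore claims a safeguard that the comparison of 271 with 272 lacks, and the sentence after it points the other way.

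Baseline BMI, the same variable as the main outcome, is slightly lower in the intervention arm. Whatever its cause, a gap in a strongly prognostic baseline measure carries into follow-up unless the analysis accounts for it. A non-significant t-test gives no protection against that.

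**Working it through.** **The plan's own figure.** Inputs from the Power calculation: 275 per group, alpha 0.05 (taken as two-sided), 0.28 SD. Power = Φ(0.28 × √(275/2) − 1.96) = Φ(3.28 − 1.96) = 0.907, which agrees with the stated 90%. The 0.45 kg/m² equivalent implies an SD of 0.45/0.28 = 1.61.

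**Selection after allocation.**
- Attenders: 271 + 272 + 92 = 635. Excluded as overweight: 92/635 = 14.5%, in line with the 15% in Enrolment.
- Low SES in any combination (Table 1): intervention 10/271 = 3.7%, control 14/272 = 5.1%, shadow control 82/664 = 12.3%.
- The two participating arms together (24/543 = 4.4%) differ clearly from the uninvited shadow group (chi-square p < 0.001) but not from each other (p = 0.54). This fits strong selection into participation. It does not show selection that differed between the two arms.

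**Baseline BMI gap (control minus intervention).**
- SE = 1.0 × √(1/271 + 1/272) = 0.0858.
- The rounded means give a gap of 0.10 and p = 0.24. The printed P = 0.12 corresponds to t = 1.557 on 541 degrees of freedom, so the unrounded gap is about 1.557 × 0.0858 = 0.134 kg/m². Rounding explains the difference, and Table 2 is not in error.
- 95% CI: 0.134 ± 1.964 × 0.0858, or about −0.03 to 0.30.

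**Carry-over in an unadjusted follow-up comparison, with no programme effect.** Formula: r × (follow-up SD / baseline SD) × gap. The correlation r is not in the article; 0.6 to 0.8 is assumed.

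| r | Carry-over, SD 1.0 at both times (kg/m²) | Share of 0.45 kg/m² | Carry-over in SD units as share of 0.28 |
|---|---|---|---|
| 0.6 | 0.134 × 0.6 = 0.080 | 18% | 29% |
| 0.7 | 0.134 × 0.7 = 0.094 | 21% | 33% |
| 0.8 | 0.134 × 0.8 = 0.107 | 24% | 38% |

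The two share columns differ because the 0.45 target rests on an SD of 1.61, whereas the observed baseline SD is 1.0. If the follow-up SD were 1.61, the carry-over would be 0.129 to 0.172 kg/m², again 29 to 38% of 0.45.

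**Gain from adjusting for baseline BMI.** The residual SD is multiplied by √(1 − r²), which is 0.80 at r = 0.6 and 0.60 at r = 0.8. The difference detectable with 90% power falls from 0.28 to 0.28 × 0.80 = 0.22 and 0.28 × 0.60 = 0.17 SD.

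**The case against.** The strongest reply is that late self-selection harms the contrast only if it depends on the arm. If families did not know their arm when they accepted, those who came forward are in effect a random split of willing families, and low uptake limits generalisability more than it biases the comparison. The article gives this some support: one uptake figure of about 21% for the two groups, 271 against 272 children, a first invitation to see a health consultant in both arms, the same overweight cut-offs, and the same message about risk. But it does not say what families knew when they accepted. So the reply shows that bias may be absent, not that randomisation excludes it.

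Three stronger readings are tempting and are not supported.
- A reader might infer that the arms were differentially selected. The BMI gap (P = 0.12) and the income difference (P = 0.07) are weak evidence, and one of 16 baseline tests reaching 0.05 is about what chance gives.
- A reader might infer that the trial will compare BMI unadjusted, or adjust only for SDQ because of the t-tests. The Power calculation names no analysis model, and Table 2 is not said to choose covariates. A model left to a fuller document is not a finding.
- A reader might turn the carry-over into a false-positive rate far above 5% by treating the whole gap as a systematic shift. Nothing shows that it is one. If the gap is chance, the unadjusted test keeps its 5% level over repeated randomisations.

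It is also fair that the authors qualify the sentence immediately and plan to describe attrition by maternal BMI, SES and birth weight.

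**Conclusion.** The sentence should not stand. Participation and the weight screen followed allocation, so randomisation does not guarantee that the 271 and 272 participants are comparable, and the article's next sentence is at odds with the claim. This follows from the stated order of events and needs no assumption. Selection bias between the arms is possible, but the article does not demonstrate it.

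The baseline BMI point is conditional. Only if follow-up BMI were compared unadjusted would about 0.08 to 0.11 kg/m² appear in the intervention's favour with no programme effect. That figure assumes a correlation of 0.6 to 0.8, an SD of 1.0 at both times, and a gap of 0.134 recovered from the printed P value, whose interval includes zero. Adjustment is worthwhile whether the gap arose by chance or by selection, since it removes the expected carry-over and gains precision. It does not remove bias from unmeasured differences between families, so the correction to the text is needed as well.

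**What to change.** 1. Replace the sentence in the Discussion with a statement that participation and the overweight screen came after allocation, so that selection bias between the arms is possible. State what families knew of their arm when they accepted.
2. Report acceptance and overweight exclusion by allocated arm, against birth weight, maternal pre-pregnancy BMI and, where it was retrieved, SES. The limitations text says these are known for non-participants too. Study design says that SES was extracted by hand and that low-SES selection was confined to one municipality, so the SES breakdown may be partial.
3. Make the primary BMI comparison adjusted for baseline BMI, age, sex and the municipality strata, fixed in advance and not chosen by baseline significance tests. If the full analysis plan already does so, a sentence saying so is enough.

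The cost is wording and analysis time. Baseline BMI, age, sex and municipality are already held, and no new measurements are needed.

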#### The control group

Children in this group were invited to see a health consultant. At the first meeting their heights and weights were measured and BMI was calculated. The same international cut-offs for overweight according to age and gender as in the intervention group were applied to the control group [10]. If a child was overweight at baseline it was excluded from the control group, and did not participate further. If a child was normal weight it was included, and hadadditional anthropometric measurements taken.

Children from the control group and their families were invited to a follow-up approximately 1½ year after the first visit, but they were not seen between baseline and follow-up.

All families that were invited to see the health consultant prior to intervention (intervention and control group) were told that their child had an increased risk of future obesity. This information may influence future health attitudes and practices, and may be considered an intervention by itself. We therefore applied a design using two control groups rather than only one, because differences in weight development between the intervention group and the control group, and hence development of overweight, could potentially be diluted as a consequence of informing the control participants that the child was predisposed to obesity.

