An additional control group (the shadow control group) was therefore chosen, where the families were unaware of whether their child was predisposed or not. Children in this group were not invited to see a health consultant, and were followed exclusively through registers. Information on height and weight was obtained from records of the general practitioners (GPs) who perform regular preventive child health examinations of pre-school children at ages 2, 3, 4, and 5 years. If a child was overweight at time of baseline, it was excluded from the study. Collection of data on height and weight from the GPs is currently on-going. However, as participation in the shadow control group is unaffected by willingness to participate (information for everyone included in this group is obtained via existing registries), differences in weight development between the intervention group and this control group and hence development of overweight, will potentially be inflated since these families do not have to actively show up to become a participant. Thus, it is likely, that the true effects of the intervention may be in the range between the effects of the intervention group compared to the shadow control group, and the intervention group compared to the control group. This use of the study design may, on the other hand, provide an additional result related to whether the simple information given to the families that their child is predisposed to future overweight, may lead to self-selected changes in lifestyle without further help (as described above), and may thus prevent the development of overweight. Hence, differences between the shadow control group and the ordinary control group in excess weight gain will also be examined.

The study is registered with ClinicalTrials.gov, ID NCT01583335.

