### Measures

From the shadow control group, information on heights and weights was collected from the journals of the GP’s (on-going July 2012). As part of the child health examinations and vaccination programs, the GP measures heights and weights at age 2, 3, 4, and 5. The examinations are free of charge, and more than 80% of all Danish children participate at each examination [11].

In the intervention and the control group, information on the following variables was obtained both before and after the intervention:

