#### Dietary measurements

The parents of each participant were asked to fill out a 4-day dietary record of their child. The parents were asked to record the dietary intake from Wednesday to Saturday. These specific days were chosen to obtain information on dietary intake in both week- and weekend days. The dietary record was accompanied by a picture book to help the families estimate portion sizes and a guidance in how to fill out the dietary record. Each dietary record was entered into Dankost 3000, a software program applied to calculate the individual intake of macro- and micronutrients.

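### The control v shadow control contrast cannot show whether risk information alone prevents overweight, because it also carries a baseline examination, parental recording, consent selection and a change of measurement source

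*Protocol article*

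**What the plan says.** The protocol article makes the claim twice. In the section on the control group, where the shadow control group is introduced, it says that the two-control design may give an extra result: whether telling families about the predisposition "may lead to self-selected changes in lifestyle without further help" and so prevents overweight. It then names the contrast: "differences between the shadow control group and the ordinary control group in excess weight gain will also be examined". The Discussion repeats this as a strength, saying that the design can answer this question: "if the simple information to parents that their child is at a high risk of future overweight, is an easy and inexpensive way" to prevent later overweight.

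The same article describes what control families received. Under the control group heading: "Children in this group were invited to see a health consultant. At the first meeting their heights and weights were measured and BMI was calculated". All families invited to a consultant, in both the intervention and the control group, "were told that their child had an increased risk of future obesity". The Measures section then says: "In the intervention and the control group, information on the following variables was obtained both before and after the intervention". That list includes "The parents of each participant were asked to fill out a 4-day dietary record of their child".

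Shadow families were not told of the risk and not invited. Their heights and weights come from GP records of the routine child examinations.

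**The concern.** An effect can be credited to information alone only if information is the one thing that differs between the groups compared. Here the informed group was also examined in person and asked to record what the child ate and how it slept, and to answer questions on activity, behaviour and parental stress. The article accepts that the risk message may act as an intervention by itself, but it does not consider that the examination or the recording might do so too.

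At stake is the conclusion that the contrast is meant to support. If controls gain less excess weight than shadow children, the article as worded would credit the message and describe it as inexpensive, although the exposure tested was message plus visit plus records in a self-selected group. A null result would not isolate the message either, because its effect could be offset or masked by the other differences.

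**Working it through.** The point is about identification, so the main check sets the two groups side by side.

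| Element | Control group | Shadow control group | Section |
|---|---|---|---|
| Told of increased risk | Yes | No | The control group |
| Health consultant visit | Yes, at baseline and at follow-up, none between | No | The control group |
| Height and weight | By consultant | By GP at ages 2, 3, 4 and 5 | The control group; Measures |
| Waist, hip, skinfolds, impedance | Yes | No | Anthropometric measurements |
| 4-day dietary record | Asked for | No | Dietary measurements |
| 7-day activity questionnaire (C-PAQ) | Asked for | No | Physical activity |
| 7-day sleep diary | Asked for | No | Sleeping habits |
| SDQ and parental stress items | Asked for | No | Stress of the child; Overall well-being of the family |
| Entry depends on willingness | Yes, about 21% took part | No | The control group; Enrolment |

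Information is one of several rows that differ. Within this contrast every other row changes together with it, so neither adjustment nor a larger sample can separate them.

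**How many controls completed the battery** (Table 2, control n = 272):
- dietary intake: 244/272 = 90%
- sleep latency: 256/272 = 94%
- SDQ: 256/272 = 94%

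The extra exposure was therefore close to universal among controls. According to the Intervention section, the consultants drew primarily on the dietary record and the parental questionnaire to judge each intervention family's needs. The instruments that controls completed thus cover the four areas that the intervention targets.

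**Sample size.** The article's only figure is 275 per group for 0.28 SD at 90% power, intervention v control. With two-sided alpha 0.05 (sidedness is not stated): n = 2 × (1.960 + 1.282)² / 0.28² = 269 per group, and power at 275 is 0.907. The statement reproduces. For control v shadow, with 272 and the expected 394 children, the detectable difference is (1.960 + z) × √(1/272 + 1/394):
- 80% power (z = 0.842): 0.22 SD
- 90% power (z = 1.282): 0.26 SD

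So the contrast has reasonable precision. The difficulty lies in what it estimates.

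**Sign of consent selection** (Table 1, any low socioeconomic status):
- shadow: 74 + 6 + 0 + 2 = 82; 82/664 = 12.3%
- control: 8 + 4 + 1 + 1 = 14; 14/272 = 5.1%; Fisher exact p = 0.0008 against shadow
- intervention: 8 + 1 + 1 + 0 = 10; 10/271 = 3.7%; p = 0.53 against control

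The two groups that needed consent resemble each other and differ from the group that did not. The 664 are the children whose GP data are being sought, and 394 are expected in the end, so this is indicative only.

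**The case against.** The contrast is secondary and cautiously worded in the section on the control group: an additional result that the design may provide. Neither the stated purposes nor the power calculation rests on it. Controls were not seen between baseline and follow-up, and no feedback or counselling is described for them, so saying that they had no further help is fair when set against up to 10 consultations plus classes. The documents give no evidence that one examination and a few days of recording change weight about 1½ years later. All of this stands, and it limits the matter to how a secondary contrast is described.

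Several stronger readings are tempting and are not supported:

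- *Controls saw a dietetics specialist.* The training in dietetics and nutrition is stated only for the intervention group's consultant. For controls the text says only health consultant.
- *Shadow children had no measurement at all.* GPs weighed and measured them at routine examinations. What they lacked was the project visit, the extended anthropometry and the recording.
- *Controls carried out extensive self-monitoring.* The diaries cover 4 and 7 days, the rest is questionnaire, and only the baseline round could affect weight at follow-up.
- *The 79% or so who declined are the true information-only group.* All invited families were told of the risk, but the article does not say when or how, so it cannot be established that non-attenders had the message before declining.
- *The contrast cleanly estimates information plus examination.* It does not, because consent selection and measurement source differ as well.

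What the objection does not answer is the Discussion, which states without qualification that the design makes this evaluation possible.

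**Conclusion.** The concern holds in limited form. The control v shadow contrast lacks the property claimed for it: it compares invitation, risk information, baseline examination and recording, taken together, with no contact. It also compares about 21% volunteers measured by consultants with children included regardless of willingness and measured by GPs. The article acknowledges the willingness difference, but only as inflating intervention v shadow. The same reasoning applies to control v shadow and is not applied there.

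The size of the resulting distortion cannot be given, because the documents contain no estimate for any component. The conclusion needs only that the components cannot be separated, which follows from the design. It assumes that controls received the baseline battery as the Measures section describes, and Table 2 supports this for 90% to 94% of them on diet, sleep and SDQ.

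A reader might infer that the main comparison is compromised. It is not: intervention and control groups had the same message, visit and baseline battery, and both depended on consent.

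**What to change.** In the section on the control group and in the Discussion, describe control v shadow as an exploratory comparison of invitation, risk information, baseline examination and recording, combined, against no contact. State in both places that it is open to consent selection and to different measurement sources (consultant v GP records), and extend to this contrast the caution already given for intervention v shadow. Remove the statement that the design evaluates simple information as a cheap preventive method, or qualify it so that it no longer attributes a difference to information alone.

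The cost is wording only: no change to data collection, sample size or the intervention v control analysis. The downside is giving up the conclusion about simple information.
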